### Sample size calculation

Sample size was calculated to estimate the occurrence of outcomes in each of the groups separately and to evaluate the association between each outcome: muscle thickness [5], IL-6 [6], TNF-alfa [7] and, quality of life [8], and the exposure variable. According to the largest sample size calculation, 36 patients would be required (to maintain a minimum power of 80% and a 95% confidence level). To compensate for possible losses and refusals, 42 patients will be included [[5], [6], [7], [8]].

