**Fig. 1 fig0005:**

Intervention schedule.

The baseline measurements will be distributed at week 1 as follows. At the 1st HD session of the week the resting HR, resting blood pressure, ankle-arm index (AAI) measurements and questionnaire application will be performed. At the 2nd HD session of the week the percentage of fat, body mass and height measures, and blood collection will be obtained, after the HD session. At the 3rd HD session of the week the functional capacity (using the 6-minute walk test) and muscle strength (using dynamometry) will be measured. The final evaluations (post-intervention) will follow the same weekly distribution of the baseline measures.

Blood pressure will be measured with an accurate analog sphygmomanometer (accuracy of 1.0 mm/Hg) and stethoscope (BD, Brazil). Body mass and height will be measured using digital electronic anthropometric scale with a resolution of 0.1 kg and 0.1 cm, respectively (Filizola, Brazil). Body mass index (BMI) will be calculated based on body mass and height. The HR will be measured using a digital HR monitor (Polar, Finland).

To calculate ankle-arm index (AAI) the patient should rest supine for at least 10 min before testing, the systolic blood pressure measurement will be performed in the upper limb using an analog sphygmomanometer. The measure will be performed on the arm that is not with the dialysis fistula. The systolic blood pressure at the ankles will be measured using the vascular Doppler with transducer of 5–8 MHz with application of gel on the analyzed region and the same model of sphygmomanometer as previously reported [9]. The cuff will be placed about three inches above the malleolus. The following formula will be applied to calculate AAI: AAI = higher ankle pressure x higher arm pressure^−1^ [9].

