**Fig. 3 fig0015:**
[figure not shown]
Training protocol.

The exercise sessions will use the following routine: 1) place the heart monitor on the chest of the subjects; 2) place the BFR equipment on their thighs while standing; 3) inflate the pressurized band to induce BFR while sitting in HD chair; 4) place the stationary bicycle in front of the patient; and 5) instruct patients to cycle.

The maximum HR will be determined using the following formula: HRmax = 211-(0.64 x age) [17]. Patients using medications influencing HR, such as beta-blockers, will have their HR corrected based on the study of Godoy [18].

A cycle ergometer will be placed in front of the patient's chair and will be positioned at a distance allowing a relative knee angle (inner angle formed between the thigh and the leg) between 150° and 155° [19].

The BFRG will perform the exercise with BFR, while the CG will perform with no BRF. For the BFRG, a 6 cm wide inflatable band will be placed at the root of the lower limbs and inflated according to the thigh circumference of the patients, as suggested by Loenneke et al. [15]. The following thigh circumference/pressure will be applied to impose 50% of arterial restriction: from 45 to 50.9 cm: 100 mmHg; to 51 from 55.9 cm: 130 mmHg; from 56 to 59.9 cm: 150 mmHg; ≥60 cm: 180 mmHg. The patient will maintain BFR throughout the exercise. The exercise will be interrupted if the patient shows any discomfort or wants to stop.

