### Data processing and analysis

The data will be doubled typed in EPIDATA 3.1 software, which will perform analysis to verify inconsistencies and correction of possible errors. The 5% significance level will be used and the statistical analysis will be conducted in Stata 14.0 software. The two mixed factors analysis of variance (ANOVA) will be used in the comparison of the training protocols, using Bonferroni as a post-hoc test for parametric variables. Kruskal-Wallis test and Dunn's post-hoc test will be used to non-parametric variables. The responsible researcher for the statistical analysis will be blinded regarding to the study objectives.

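### Six extra patients protect power but not against unequal loss, and end measures tied to the intervention may leave early stoppers mistimed or unmeasured

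*Protocol article*

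**What the plan says.** **Losses.** The section on sample size calculation states: "According to the largest sample size calculation, 36 patients would be required". It then adds: "To compensate for possible losses and refusals, 42 patients will be included". No other sentence in the article deals with patient loss.

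**Analysis.** The section on data processing and analysis states: "The two mixed factors analysis of variance (ANOVA) will be used in the comparison of the training protocols". Bonferroni is the post-hoc test, with Kruskal-Wallis and Dunn's test for non-parametric variables. "The 5% significance level will be used". The abstract says that baseline measures are compared with final measures.

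**Timing.** Under Procedures: "The final evaluations (post-intervention) will follow the same weekly distribution of the baseline measures". The same section places blood draws after the third session and after the last session of each mesocycle, at the end of weeks six and twelve. The last draw comes 48 hours after the last exercise session.

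**Interruption.** The intervention description has BFRG patients keep the restriction on for the whole exercise, then says: "The exercise will be interrupted if the patient shows any discomfort or wants to stop".

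**The concern.** Adding patients corrects the loss of precision caused by dropout. It does nothing for bias when the patients lost from one arm differ from those lost from another. Unequal loss is plausible here: the control group has nothing to stop, EG cycles, and BFRG cycles with inflated thigh cuffs in an open-label trial.

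The written schedule adds to the exposure. Week numbers and training sessions coincide only for patients who train to the end. For someone who stops in week 4, say, a draw 48 hours after the last session falls about two months early, or is not defined. The session anchor does not fit the control group either, as it has no exercise session. A later analysis plan cannot recover values that were never collected at the right time.

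The article's Design section speaks of effectiveness, and its Discussion of implementing exercise with BFR during haemodialysis. For that question, patients who cannot tolerate BFR belong in the result.

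**Working it through.** **1. The plan's own figures.** 42 − 36 = 6 extra, or 2 per arm. Then 1 − 36/42 = 14.3% loss, or 42/36 − 1 = 16.7% if the allowance is added to 36. Either reading is coherent. The 36 cannot be reproduced, because the article gives no effect size or SD. Back-solving with 12 per arm, two-sided 5% and 80% power gives d = √(2/12) × (1.960 + 0.842) = 1.14.

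**2. What the extra patients protect.** At d = 1.14 (normal approximation), power against a 12-patient arm is 80% with 12 in the other arm, 76% with 10 and 71% with 8. The allowance guards against this fall in power and nothing else.

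**3. Bias if stoppers have no final value.** Let k of 14 BFRG patients be lost (42/3 = 14 per arm, assuming an equal split). Let δ be the shortfall of stoppers against completers, in SD of the change. The full-arm mean is the weighted mean of the two groups, so the completers' mean exceeds it by (k/14) × δ.

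**4. False-positive rate with no true effect.** BFRG completers (n = 14 − k) are compared with a full arm of 14 by a t test with unit SD. The noncentrality is (k/14)δ / √(1/(14 − k) + 1/14), with 26 − k degrees of freedom. The Bonferroni level for three pairwise comparisons is 0.05/3 = 1.67%.

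| k lost in BFRG only | Bias, δ = 0.5 to 1.0 SD | Rejection, 5% unadjusted | Rejection, 1.67% Bonferroni |
|---|---|---|---|
| 2 | 0.07 to 0.14 SD | 5.3% to 6.4% | 1.8% to 2.3% |
| 4 | 0.14 to 0.29 SD | 6.3% to 10.1% | 2.3% to 4.2% |
| 6 | 0.21 to 0.43 SD | 7.5% to 15.1% | 2.8% to 6.8% |

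Example, k = 6 and δ = 1.0: bias = 6/14 = 0.429 and √(1/8 + 1/14) = 0.443, so the noncentrality is 0.967 with 20 degrees of freedom. The two-sided rejection rate is 15.1% at the 5% critical value and 6.8% at the Bonferroni one. The values of k and δ are assumptions. k = 6 places the whole trial's allowance in one arm.

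**5. Direction.** In 40,000 simulated trials with 14 per arm and no true effect, the k least tolerant BFRG patients were removed (k = 2, 4, 6). The bias depends on the assumed correlation between tolerance and outcome change:

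- correlation 0.3: +0.07, +0.14, +0.20 SD
- correlation 0.7: +0.17, +0.31, +0.46 SD
- correlation 0: none
- correlation −0.3: −0.07, −0.13, −0.19 SD, against BFR
- equal loss in both exercise arms: about zero at every correlation

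**6. Which outcomes are exposed.** Six of the 11 dependent variables in Table 1 are blood markers, with draws between baseline and final. The schedule gives the other five (muscle thickness, ankle-arm index, walk test, strength, quality of life) only baseline and final values. For these five, a patient without a final value adds nothing to the group-by-time contrast.

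**The case against.** A reader might infer that the plan commits the trial to a completers-only comparison that favours BFR. The article does not support this.

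- **Completers only.** No sentence excludes patients who stop. The interruption sentence concerns stopping exercise, not leaving the trial or missing the final week, and it is not expressly limited to BFRG. The control group has final measures too, so the post-intervention label must work as a calendar time for at least that arm, and the draws at weeks six and twelve carry week numbers. Patients who stop cycling would normally still attend the unit for dialysis.
- **Favours BFR.** This needs more loss in BFRG than in the comparator and poorer outcomes among those lost. The article gives neither, and step 5 shows that the bias can vanish or reverse.
- **Size.** The unadjusted error rates ignore the planned Bonferroni test. With it, the rate exceeds 5% only in the extreme corner (6 lost, 1.0 SD). With 2 lost, the even share of the allowance, inflation is small.
- **Omission.** Analysis population and missing-data rules are commonly left to a full protocol or analysis plan, and neither is shown. Their absence is no error.

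All of this stands. It does not answer the points that rest on stated text: the allowance covers power only, the named ANOVA classically needs complete visits, and the end measures are anchored to the intervention or last session instead of allocation.

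**Conclusion.** The point holds as an exposure created by stated methods, not as a demonstrated bias. With about 14 per arm, losing 2 to 6 patients from BFRG alone, with stoppers 0.5 to 1.0 SD worse, would overstate the BFR contrast by 0.07 to 0.43 SD. The pairwise false-positive rate would be 5.3% to 15.1% at an unadjusted 5%, or 1.8% to 6.8% against 1.67% under Bonferroni. These figures rest on assumed loss, an assumed deficit, no loss in the comparator and no final value for stoppers. The direction is conditional. What does not depend on those assumptions is that six extra patients cannot correct unequal loss, and that the session-based timing is ill-defined for anyone who stops early. The change is cheap enough to be worth making.

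**What to change.** 1. Schedule the week 6 blood sample and the final assessment week by calendar time from allocation, for every randomised patient who still consents, whether or not still exercising. Reconcile this with the wording that times the last draw from the last exercise session, and state how it applies to the control group.
2. Analyse all patients in the arm allocated.
3. Replace the mixed ANOVA with a linear mixed model on all available visits. The gain is mainly for blood markers, which have intermediate samples. For outcomes with only baseline and final values the model recovers little, and it does not repair loss that depends on the unseen outcome. Continued assessment (item 1) is the essential part.
4. Report stopping of exercise, with reasons, by arm and separately from leaving the trial.

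The rule for interrupting exercise need not change. The cost is a few sentences of protocol text, a standard mixed-model command in the Stata software already planned, and assessments at dialysis visits that patients normally still make. The downside is a little more analysis work and possibly a smaller BFR effect estimate than among completers.

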### Recruitment

Subjects will be recruited at the nephrology department, all chronic patients of the unit who is on hemodialysis treatment will be investigated in your medical records and basic information will be analyzed allowing the application of some exclusion criteria. Afterward, they will be individually interviewed and only who fill all criteria to be included, invited to participate in the study. Then, the goals of the study will be explained and the permission to perform the intervention will be solicited.

### Randomization

The randomization process will be performed using the generation of random numbers in the Stata software, version 13, and the researcher who will carry out the process will be blinded regarding to the study objectives. The randomization will be done in blocks, each block referring to the HD shift. In each block, the first patient drawn will go to the BFRG, the second to the EG, the third to the CG, and so on. In total, 14 patients will be drawn in each block to ensure balance between groups.

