**Fig. 2 fig0010:**
[figure not shown]
Schedule of blood collections.

Serum levels of IL-6, IL-10, and CRP will be measured using immunoassay kit (DuoSet ELISA Development, R&D Systems, Inc., USA). These methods will follow the manufacturer's recommendations. The amount of IL-6, IL-10, and CRP will be determined by measuring the absorbance at 450 nm. All samples and standards will be measured in duplicate, and the coefficient of variation will be less than 5%. The IL-6, IL-10, and CRP levels will be expressed in pg/mL.

Oxidative stress markers (catalase, peroxide dismutase, and glutathione peroxidase enzymes) will be measured using a commercially available kit (RANSEL®; Randox Lab, Antrim, United Kingdom), using the method described by Misra and Fridovich [12].

The 6-minute walk test will be conducted on a 30-meter flat track, demarcated every three meters. Before starting the test, patients will remain seated for 10 min to stabilize vital signs. The patient will be advised to walk for 6 min, from one end of the lane to the other, at the highest possible speed. This test will be performed before the HD session, since patients cannot walk well after the HD session due to the loss of fluid with hypotensive effects [13].

The static strength testing of lower limbs will be performed with a Crown® brand dynamometer. Initially, patients will be instructed to stand on the base of the device, flexed knees forming an angle of approximately 120°, upright spine, arms along the body and extended elbows. After resetting the instrument, the subjects should perform the maximum knee extension force possible, avoiding any movement with the spine or arms and moving the body backwards. Two measurements will be performed with a 1 min interval between them. The mean of these two measures will be used as a result [14].

After baseline collection, participants will be allocated randomly: 1) BFRG; 2) EG; 3) CG. The intervention will last twelve weeks divided into three weekly sessions, always having at least a day interval between sessions. All physical exercise sessions will be monitored by physical therapists and physical education teachers to guarantee the perfect execution of the exercises and the correct use of the BFR accessory and heart monitor.

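### Fourteen patients per shift, rotated over three arms from a fixed start, cannot give the balanced groups claimed: each full shift splits 5/5/4, always short in the control group

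*Protocol article*

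**What the plan says.** The Randomization section of the protocol article fixes three things.

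- The block is the shift: "The randomization will be done in blocks, each block referring to the HD shift".
- The assignment rule is a fixed rotation that begins with the same arm each time: "In each block, the first patient drawn will go to the BFRG, the second to the EG, the third to the CG, and so on".
- The block size and its purpose: "In total, 14 patients will be drawn in each block to ensure balance between groups".

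The Sample size calculation section gives the totals: "According to the largest sample size calculation, 36 patients would be required", and then "To compensate for possible losses and refusals, 42 patients will be included". The stated targets for the 36 are "to maintain a minimum power of 80% and a 95% confidence level".

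The article does not state the number of shifts, a target number per arm, or a loss rate.

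**The concern.** The number 14 is justified by balance between groups, but a rotation over three arms balances only when the number drawn is a multiple of three. Because the rotation begins again at BFRG in every shift, the imbalance does not average out over shifts. It accumulates in one arm, the control group.

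Two things are at stake. The allocation procedure does not do what its own sentence says. And the six patients added to the required 36 may all end up in the exercise arms, so that the comparator for the exercise effect has little or no margin for dropout.

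**Working it through.** **Inputs from the protocol article.** Three arms, 14 patients per block, block = shift, rotation BFRG-EG-CG restarting at BFRG (Randomization); 36 required, 42 included, 80% power, 95% confidence (Sample size calculation).

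**Assumptions needed beyond the text.** Three shifts; 36 split as 12 per arm; a loss rate equal to the one implied by 36 and 42; a two-sided 5% level.

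**1. The plan's own totals.** 42/14 = 3 blocks, so 14 per shift fits a total of 42 if there are three shifts. Two shifts would give 28 patients and four would give 56. Going from 36 to 42 implies a loss of 1 − 36/42 = 14.3%. The 36 itself cannot be reproduced, because the article gives no effect size, standard deviation or test for it.

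**2. One block.** 14 = 4 × 3 + 2. Four full turns give 4/4/4, and the two remaining patients go to BFRG and EG. Each full block is therefore 5/5/4. This step needs no assumption about the number of shifts.

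**3. Three blocks.**

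| | BFRG | EG | CG |
|---|---|---|---|
| Rule as written, 3 × (5/5/4) | 15 | 15 | 12 |
| Equal split of 42 | 14 | 14 | 14 |
| Equal split of 36 | 12 | 12 | 12 |
| Reserve, rule as written | 3 | 3 | 0 |
| Reserve, equal split | 2 | 2 | 2 |

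**4. Precision.** The variance of a difference between two arms is proportional to 1/n1 + 1/n2.

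- Exercise arm versus CG: 1/15 + 1/12 = 0.150, against 2/14 = 0.143. The ratio is 1.05, so the variance is 5% larger and the standard error about 2.5% larger.
- BFRG versus EG: 2/15 = 0.133, against 0.143. The ratio is 14/15 = 0.93, so the variance is about 7% smaller.

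**5. Power for an exercise arm versus CG.** Normal approximation for two means, with the standardised effect d set so that 12 versus 12 gives 80%: d = (1.960 + 0.842) × √(2/12) = 1.144. Power = Φ(d/√(1/n1 + 1/n2) − 1.960).

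| | Rule as written | Equal arms |
|---|---|---|
| Before losses | 15 v 12: 84.0% | 14 v 14: 85.7% |
| After 14.3% loss in every arm | 12.9 v 10.3: 78.1% | 12 v 12: 80.0% |

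The cost is 1.7 points before losses and 1.9 points after. The value of d only calibrates this comparison; it is not a figure from the article.

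**6. Check of possible repairs.**

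- Each arm starts one of three shifts of 14: 5/5/4, 4/5/5 and 5/4/5. BFRG 5 + 4 + 5 = 14, EG 5 + 5 + 4 = 14, CG 4 + 5 + 5 = 14.
- Rotation carried on across shifts without restarting: 42/3 = 14 full turns, so 14/14/14 whatever the size of each shift.

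**The case against.** The strongest reply is that this is a slip of wording. Since 42/3 = 14, the authors probably meant 14 per group, and the stated aim of balance fits that reading. This is plausible, but the sentence says 14 per block and the section defines the block as the shift. If 14 per group was meant, the sentence still has to be corrected. A second reply, that the rotation runs on from one shift to the next, would give 14/14/14, but the text restarts it in each block.

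The objection that the effect is small stands. About 2 points of power are lost against the control group. The comparison that isolates blood flow restriction, BFRG versus EG, gains precision, and the Design section gives evaluation of that intervention as the purpose. A split of 5/5/4 is also as near to balance as 14 patients allow.

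A reader might infer more than the article supports in three ways:

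- **That 15/15/12 is the planned allocation.** The number of shifts is not stated; three comes only from 42/14.
- **That the control group certainly has no allowance for losses.** This needs 36 to mean 12 per arm, which is natural but unstated. The extra six also cover refusals as well as losses. Invitation and consent come before allocation (Recruitment and Procedures: "After baseline collection, participants will be allocated randomly: 1) BFRG; 2) EG; 3) CG"), so part of the six may be used up before anyone is assigned. An after-allocation reserve of 2/2/2 is therefore itself an interpretation.
- **That the comparison is biased.** Modestly unequal arms cost precision; they do not by themselves bias a randomised comparison.

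**Conclusion.** The concern holds as an internal contradiction. The written rule yields 5/5/4 in every full shift, always short in the control group, so it does not deliver the balance for which 14 was chosen. That much rests only on the article's own figures.

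The totals of 15/15/12 depend on three shifts. The reserve of 3/3/0 depends also on 12 per arm. Under those assumptions and a 14.3% loss in every arm, power against control is 78.1% instead of 80.0%, just under the stated minimum. The calculation assumes that the sample size was set for a two-arm comparison, which the article does not say.

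The point should be fixed, but it does not threaten the validity of the trial. It matters mainly because it is cheap to put right before allocation and cannot be undone afterwards.

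**What to change.** First, state in the Randomization section whether 14 is the number per group or per shift, and give the number of shifts. Then:

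- **If 14 is per group:** correct the sentence, and give the number to be drawn per shift and how the rotation runs over shifts.
- **If 14 is per shift over exactly three shifts:** let each arm start the rotation in one shift, with the order of starting arms drawn at random. The result is 14/14/14.
- **If the number of shifts or their sizes differ:** carry the rotation on from one shift to the next instead of restarting it at BFRG. Forty-two patients then still give 14/14/14.

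A number per shift divisible by three would also balance each shift, but over three shifts it changes the total: 12 per shift gives 36 patients and 15 gives 45. The options above keep 42.

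The cost is a sentence or two in the protocol and one line in the allocation code, with no added patients.

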### Procedures

Immediately after recruitment, all enrolled patients who agree to participate in the study will sign the informed consent form. The subjects will then proceed to the baseline data collection, intervention protocol and final assessments, respectively (Fig. 1).

